### Interventions

#### Interventions

Participants will be randomly assigned to either control or one of the experimental groups with a 1:1 allocation as per a computer-generated randomization schedule stratified by children’s age using five permuted blocks of 6 participants.

**GROUP 01:** 30 participants. Conventional treatment, without complementary treatment. Bi-monthly consultations with a child and adolescent psychiatrist, including drug treatment if there is a clinical indication (at medical discretion, according to the clinical protocol), and without any other type of complementary treatment.

**GROUP 02:** 30 participants. Conventional treatment and behavioral intervention in face-to-face format. Bi-monthly consultations with a child and adolescent psychiatrist, including drug treatment if there is a clinical indication (at medical discretion, according to the clinical protocol), and complementary behavioral intervention: parent management training, in face-to-face format, with a specialized therapist, in six sessions held on a weekly basis, adapted from the “Parent Management Training” manual developed by Alan Kazdin [22].

**GROUP 03:** 30 participants. Conventional treatment and behavioral intervention in online format. Bi-monthly consultations with a child and adolescent psychiatrist, including drug treatment if there is a clinical indication (at medical discretion, according to the clinical protocol), and complementary behavioral intervention: parent management training, in online format, on a platform developed for the study, in six modules, to be carried out on a weekly basis, adapted from the “Parent Management Training” manual developed by Alan Kazdin [22].

The parent training will be carried out following the model proposed by Kazdin [22], adapted from 12 to 6 sessions (more extensive), and excluding those stages where the child’s presence was requested (see Fig 1), in order to make this project feasible for low-income families. Face-to-face version will be carried out individually in a weekly-based 6 sessions guided by a specialized therapist. PT online will have 6 modules, whose objectives will be analogous to those of face-to-face sessions. In online version, parents will have access to videos in animations or recordings, that must be seen sequentially and considering one module per week. Parents should watch all videos available for each module, with an approximate duration of 30 minutes in total, and they may be watched more than once. At the end of each module, a summary booklet will be made available for download, in addition to other necessary support materials according to the topics covered in the module (a sheet for recording the behavior of the child, for example). In online version, parents will have no contact with the therapist and they should answer some questions about what was addressed in that module, reaching 60% of correct answers to access the next module. In face-to-face version, the summary booklet and others support materials made available will be the same as the online format.

**Fig 1 pone.0272516.g001:**
[figure not shown]
Parent training sessions/modules. Intervention adapted from the “Parent Manegement Training” manual developed by Alan Kazdin (2005).

The face-to-face intervention will be carried out by psychologists from the Research Center of Impulsivity and Attention (NITIDA), previously trained and with at least five years of experience in behavioral psychology.

#### Modifications

The participant will be excluded from the survey if he does not attend or does not watch regularly the weekly sessions of the intervention. If the patient reports the impossibility of attending the session and is available to reschedule it within a maximum of 30 days, or in the case of the online group, watch the content up to a maximum of 30 days after the scheduled date, the patient can proceed with the intervention. The intervention does not offer any type of risk to the patient, and therefore discontinuity is only related to attendance.

Participants whose diagnosis on screening differs from the diagnosis of the psychiatry team will be excluded from the study.

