#### Concomitant care

Treatment as usual will be delivered for all patients, including drug treatment if there is a clinical indication (at medical discretion, according to the clinical protocol). The treatment can also include speech therapy and occupational therapy, if there is a clinical indication. Other behavioral interventions concurrently will not be allowed.

Although the psychiatric consultations offered by Research Center of Impulsivity and Attention (NITIDA) start at the same time as the first assessment before behavioral intervention, some children may eventually already be on medication or other non-pharmacological treatment. The study will report these treatments, but only participants with another behavioral intervention at the same time will be excluded.

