#### Implementation

All patients who give consent for participation and who fulfil the inclusion criteria will be randomized. Randomization will be requested by the staff member responsible for recruitment and clinical interviews and will be performed by the computer technician, both members of NITIDA. In return, the computer technician will send an answer form to the study therapist who is not involved in assessing the outcome of the study. This form will include a randomization number. Closed envelopes with printed randomization numbers on it will be available for the therapist. For every randomization number the corresponding code for the therapy group of the randomization list will be found inside the envelopes. The therapist will open the envelope and will find the treatment condition to be conducted in this patient. The therapist then gives the information about treatment allocation to the patient. Staff responsible for recruitment and symptom ratings is not allowed to receive information about the group allocation.

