#### Retention

The intervention has the potential to bring great benefits to the whole family and parents will be encouraged weekly through teasers received via email and WhatsApp to complete the process. Moreover, a report containing the child’s intelligence and behavior assessment will be given to the parents. In addition, all children will be under medical supervision at the outpatient clinic (NITIDA) and doctors also recommend the continuity and completion of the intervention as a complementary treatment. Access to families is easy and if parents leave the PT, all post-intervention measures will be collected as soon as the dropout is confirmed (according to the treatment interruption criterion).

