### Auditing

Not applicable. The diagnosis divergence will be evaluated and informed on a weekly basis.

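### Two exclusion rules, for diagnostic divergence and for concurrent behavioural therapy, are not confined to the time before randomisation, so randomised children can be removed on information that may depend on arm

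*Protocol article*

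**What the plan says.** All statements are in the protocol article.

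- **Modifications** (under Interventions), after the attendance rules: "Participants whose diagnosis on screening differs from the diagnosis of the psychiatry team will be excluded from the study".
- **Concomitant care**: "Other behavioral interventions concurrently will not be allowed". After noting that some children may already be on medication or other treatment, it adds that "only participants with another behavioral intervention at the same time will be excluded". It also says that the psychiatric consultations "start at the same time as the first assessment before behavioral intervention".
- **Interventions**, for all three groups: "Bi-monthly consultations with a child and adolescent psychiatrist".
- **Implementation** (under Allocation): "All patients who give consent for participation and who fulfil the inclusion criteria will be randomized". The Eligibility criteria do not mention agreement by the psychiatry team or the absence of another behavioural intervention.
- **Auditing**: "The diagnosis divergence will be evaluated and informed on a weekly basis". Divergence is also mentioned under Formal committee and under Interim analyses.
- **Trial design** calls the trial open. **Blinding** lists data management, the statistician, and recruitment and assessment staff as blind. The treating psychiatrists are not named there.
- **Retention**: "doctors also recommend the continuity and completion of the intervention as a complementary treatment".

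**The concern.** Randomisation makes the arms comparable only if membership of the analysed groups is fixed by information that the arm cannot influence. An exclusion settled before allocation meets that condition. The same exclusion applied afterwards may not, if the person deciding knows the arm or if the arm affects the event that triggers it.

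Both triggers could be affected. The psychiatry diagnosis concerns the same ADHD and ODD symptoms that form the primary outcome, and the K-SADS-PL interview is both the screening instrument and a primary outcome measure. Families in Group 1 are offered no complementary behavioural treatment, so they may have more reason to look for it elsewhere.

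These rules are separate from the exclusion for poor attendance or non-completion. Repairing that one would leave these two in place.

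**Working it through.** **1. Can the rules act after randomisation?**

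| Feature of the article | Points to |
|---|---|
| Divergence rule sits under Modifications, beside the attendance rules, and not under Eligibility criteria | after |
| Implementation randomises on consent and inclusion criteria only | after is possible |
| Divergence appears under Formal committee, Interim analyses and Auditing (weekly) | continuing review |
| Consultations are part of the treatment in every arm | contact continues |
| Consultations start with the first assessment | before |
| Modifications says discontinuity relates only to attendance | before, or a contradiction with the next paragraph |
| The other-therapy sentence follows one on treatments already in use | before, at least in part |

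Allocation is revealed when the intervention is about to begin (Concealment mechanism). The intervention takes six weeks (42 days), and the post-assessment may follow up to 60 days later (Data collection methods). That leaves up to 42 + 60 = 102 days between allocation and outcome, before any rescheduling of up to 30 days. A psychiatric consultation in that window is to be expected in many families. Nothing in the article closes either rule at randomisation.

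**2. Can the reason depend on arm?** The trial is open, families know their arm, the psychiatry team is not on the blinded list, and doctors are said to encourage completion of the intervention. Knowledge of allocation is plausible but not stated.

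**3. How much could it matter?** The article gives no divergence rate, no rate of other therapy and no outcome gap. The inputs below are assumptions, except the 30 per arm.

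- *p* = share of one arm removed, 10–20%, with none removed from the comparator.
- *g* = baseline-adjusted outcome gap between removed and retained children, 0.5–1.0 SD.
- *r* = correlation between baseline and follow-up, 0.6; two-sided 5% test; no true difference.

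The full-arm mean is (1 − p) × retained mean + p × removed mean. The retained mean therefore differs from it by p × g.

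- Lower end: 0.10 × 0.5 = 0.05 SD.
- Upper end: 0.20 × 1.0 = 0.20 SD.

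Standard error with baseline adjustment: SE = √[(1/n₁ + 1/n₂)(1 − r²)], with 1 − 0.36 = 0.64.

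- Lower end, 27 v 30: √[(1/27 + 1/30) × 0.64] = 0.212. P(Z > 1.96 − 0.05/0.212) = P(Z > 1.72) ≈ 4%.
- Upper end, 24 v 30: √[(1/24 + 1/30) × 0.64] = √0.048 = 0.219. P(Z > 1.96 − 0.20/0.219) = P(Z > 1.05) ≈ 15%.
- Upper end without baseline adjustment (r = 0): SE = √0.075 = 0.274. P(Z > 1.96 − 0.73) = P(Z > 1.23) ≈ 11%.

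The reference value in each case is 2.5% in that direction.

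**4. Loss of precision alone.** If 3 of 30 were lost in every arm for reasons unrelated to arm, the SE would grow by √(30/27) = 1.054, about 5%. That is minor; the issue is bias.

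**The case against.** The strongest reply is that the divergence rule only confirms eligibility. It compares the screening diagnosis with the psychiatry team's and does not speak of a new diagnosis after treatment. Consultations begin at the first assessment, and allocation is withheld until baseline measurements are complete. About six new patients are screened each week (Recruitment), so a weekly divergence review fits a review of new screens. The other-therapy sentence can be read as an entry criterion. The section on analysis population and missing data names neither reason.

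Much of this stands. A reader might infer that unblinded psychiatrists re-diagnose children according to their response to treatment and so decide who is analysed. The article does not support that. No section says that the psychiatry team learns the allocation: Concealment mechanism names only participants and therapists as learning it. No section says that children are re-diagnosed after a response. Nor does it say that other-therapy exclusions will fall mainly on controls, since the prohibition covers every arm.

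What does not stand is the step from may be settled early to is settled early. Implementation does not require psychiatric agreement, and the rule's placement and the continuing review leave later use open. A child excluded from the study is also lost to the analysis, whether or not the analysis section repeats the reason. Nor is this a detail that a condensed article merely leaves to a fuller document: the exclusion rule is stated, and stated without a limit.

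**Conclusion.** The point holds in this form: as written, both rules allow randomised children to be removed on information that may depend on arm, because neither is tied to the time before allocation or to an assessor blind to allocation. That removal will occur after randomisation, or with knowledge of the arm, is not established.

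The size is unknown. On the assumed inputs, with removal confined to one arm, the shift is 0.05–0.20 SD, and the false-positive rate in one direction rises from 2.5% to between about 4% and about 15% at r = 0.6. These rates apply to a test of difference, such as training against standard care. For the equivalence comparison of the two formats the same shift could act in either direction, and the article gives no margin against which to judge it. If divergence and other therapy are settled before allocation, the bias does not arise and only the wording needs attention. The change is worth making before the analysis because it is cheap and removes the question.

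**What to change.** 1. Add to the Eligibility criteria that the screening diagnosis and the psychiatry team's diagnosis agree, and that the child has no other behavioural intervention. State under Implementation that both are recorded before the allocation envelope is opened.
2. Reword Modifications and Concomitant care so that neither rule removes a child from follow-up or analysis after randomisation. Reconcile the Modifications text that ties discontinuity to attendance alone with the diagnosis-based exclusion that follows it.
3. After randomisation, keep every child in follow-up and in the primary analysis as allocated. Record later diagnostic divergence and other behavioural interventions by arm as protocol deviations, and use them only in a sensitivity analysis.
4. Limit the weekly divergence review to children not yet randomised, or state that after randomisation it serves recording only.

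The cost is wording, plus a short wait for the psychiatric opinion in some families. Because consultations already start with the first assessment, no extra visit should be needed in most cases.

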#### Adherence

The use of the platform is monitored, and the authors are notified at each stage completed by the participant. One day before the appropriate date for the execution of each module (a week apart between them) the platform automatically sends an e-mail, with the intention of reminding the participant of the commitment to the intervention and already anticipating a little of what will be seen in the next module (teaser). In addition, telephone contacts, when made available by the participant, enable direct contact if a delay in the deadlines is identified. Likewise, in the case of face-to-face meetings, the patient will be contacted frequently.

#### Concomitant care

Treatment as usual will be delivered for all patients, including drug treatment if there is a clinical indication (at medical discretion, according to the clinical protocol). The treatment can also include speech therapy and occupational therapy, if there is a clinical indication. Other behavioral interventions concurrently will not be allowed.

Although the psychiatric consultations offered by Research Center of Impulsivity and Attention (NITIDA) start at the same time as the first assessment before behavioral intervention, some children may eventually already be on medication or other non-pharmacological treatment. The study will report these treatments, but only participants with another behavioral intervention at the same time will be excluded.

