Considering the functional impact that disruptive behaviors add to ADHD, we will investigate the feasibility and effectiveness of a fully virtual parent training program when compared to face-to-face PT. Moreover, to assess the importance of this treatment, outcomes of intervention groups will be compared with a naive third group of children. The present study protocol has the potential to develop an accessible intervention technology aimed at families, of low/medium socioeconomic level, of children with serious externalizing problems. Socioeconomic level and organization of family environment are moderators of ADHD symptoms, demonstrating the importance of the interaction between genetics and environment in the clinical presentation/severity of the disorder [35]. This relationship can also occur due to the difficulty of access to health services, faced by low-income families. The trial, therefore, can reach vulnerable and unassisted populations. Although PT is costly in economic and human resources, it seems to have important and positive effects on the development of children [23].

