#### Choice of comparators

Parent training as proposed by Kazdin is originally delivered in face-to-face format, being a well-consolidated and evidence-based program [22]. Thus, the online format is a new proposal and its effectiveness in relation to the traditional format should be investigated. Likewise, the potential benefit of an online PT in relation to conventional treatment, which would not include this type of intervention, should be explored, since the program can bring benefits regardless of the effectiveness in relation to the traditional delivery format. All patients will be under psychiatric follow-up at the Research Center of Impulsivity and Attention (NITIDA) and therefore will be receiving conventional treatment, which especially includes pharmacological treatment, at medical discretion, according to the clinical protocol. One group will receive only the usual care, and the other two will be submitted to PT, one in online format and the other in face-to-face format.

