## Methods: Assignment of interventions

### Allocation

#### Sequence generation

Participants will be randomly assigned to either control or one of the experimental groups with a 1:1 allocation as per a computer-generated randomization schedule. The allocation sequence will be generated applying a permuted block design with random blocks, stratified by children’s age. Throughout the study, the randomization will be conducted by the computer technician without any influence of the principal investigators, raters or therapists.

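### Medication status at entry is mixed, but adjustment of the analysis is left to preliminary data instead of being fixed in advance

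*Protocol article*

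**What the plan says.** All references are to the protocol article.

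- **Who enters.** Concomitant care says that "some children may eventually already be on medication or other non-pharmacological treatment. The study will report these treatments". The same sentence goes on to say that "only participants with another behavioral intervention at the same time will be excluded". Being on medication is thus no bar to entry.
- **When clinic care begins.** The clinic's psychiatric consultations "start at the same time as the first assessment before behavioral intervention". Choice of comparators gives every arm "conventional treatment, which especially includes pharmacological treatment, at medical discretion".
- **Randomisation.** Sequence generation and Interventions name one factor: the schedule is "stratified by children’s age".
- **Adjustment.** Additional analyses makes subgroup and adjusted analyses contingent on preliminary data. Its examples are parent or child IQ, socioeconomic variables and ADHD subgroups. Medication is not among them, nor among the moderators listed under Objectives.
- **The control arm.** Background and rationale says that "outcomes of intervention groups will be compared with a naive third group of children". The Abstract, Choice of comparators and Interventions describe the same arm as standard or conventional care, with drug treatment where indicated.

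**The concern.** Two kinds of children are randomised. Those already medicated have a baseline score measured on treatment. The others have a baseline score measured just as psychiatric care begins, so their scores may fall over the pre-post window because a drug was started. The primary outcomes are ADHD and ODD symptoms on MTA-SNAP-IV and K-SADS-PL, and the Background itself names drug treatment beside parent training as effective on externalizing behaviour. Entry medication is therefore a plausible predictor of the outcome, and it can be known before allocation.

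If such a factor is left out of the model, its variation stays in the error term. If instead the decision to include it is taken after looking at the data, the choice can follow the result. Both matter with 30 per arm, and more so in a trial described as an equivalence trial, where the width of the interval largely decides the conclusion.

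The naive label is a smaller matter, but it conflicts with the arm as defined elsewhere.

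**Working it through.** The plan gives no figure on medication at entry, so there is none to reproduce. The check asks how much precision a fixed covariate would recover.

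**Inputs**
- n = 30 per arm (Interventions).
- p = proportion medicated at entry. Not given; assumed 0.5, with 0.2 as a second case.
- g = difference in post score, given baseline, between children medicated and not medicated at entry. Not given; assumed 0.3, 0.5 and 0.8 SD.
- Residual variance after baseline adjustment, within medication groups. Assumed 0.64, which is what a pre-post correlation of 0.6 gives (1 − 0.6² = 0.64).

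**Precision**
- Variance added by the omitted factor = p(1 − p)g².
- Standard error ratio, adjusted to unadjusted = √(0.64 / (0.64 + p(1 − p)g²)).
- 95% half-width of a pairwise contrast = 1.96 × √(variance × 2/30) = 0.506 × √variance.

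With p = 0.5:

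| g (SD) | Added variance | Total variance | SE ratio | SE reduction | Half-width unadjusted | Half-width adjusted |
|---|---|---|---|---|---|---|
| 0.3 | 0.0225 | 0.6625 | 0.983 | 1.7% | 0.412 | 0.405 |
| 0.5 | 0.0625 | 0.7025 | 0.954 | 4.6% | 0.424 | 0.405 |
| 0.8 | 0.1600 | 0.8000 | 0.894 | 10.6% | 0.453 | 0.405 |

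With p = 0.2, p(1 − p) = 0.16. The added variances are 0.0144, 0.0400 and 0.1024, and the reductions are 1.1%, 3.0% and 7.2%. The 50% case is therefore the one most favourable to adjustment.

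**Chance imbalance**
- The SD of the between-arm difference in proportion medicated, at p = 0.5, is √(2 × 0.25/30) = 0.129.
- With g = 0.8, 95% of randomisations shift a pairwise contrast by no more than 1.96 × 0.129 × 0.8 = 0.20 SD.
- This is a component of the unadjusted interval: √(0.405² + 0.202²) = 0.453, the half-width already in the table.
- By simulation, at p = 0.2, 0.3 and 0.5, the chance that some two of the three arms differ by at least 20 percentage points is 17%, 27% and 33%. Visible imbalance would be common, and that is when a choice of covariates made after seeing the data is most exposed to criticism.

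**The case against.** - **A reader might infer that medication status will only be reported and kept out of the analysis.** The text does not say so. In Concomitant care the word "only" limits who is excluded, and the adjustment examples are illustrative.
- **A covariate list normally belongs in the analysis plan, which is not shown.** That is right, and a missing list alone would be no finding. What stands is that the protocol does state a rule, and the rule is data-dependent. The Blinding section keeps the statistician blind to the type of intervention, which reduces the scope for steering the choice. It does not remove it, because choosing covariates on observed differences can still move the estimate.
- **A reader might infer that imbalance adds up to 0.20 SD of error, as large as the smallest effect named under Sample size.** It does not. Under randomisation its expected bias is zero, and the usual standard error already contains it. This holds for the arms as randomised; the planned exclusion of non-completers is a separate matter.
- **A reader might call medication a strong known predictor.** The documents give no effect size. At the low end of the assumed range the gain is under 2%.
- **A reader might take the naive label to mean training versus no treatment.** The sentence is about the value of parent training, so naive to training is the natural reading. Interventions also defines the arm as conventional treatment "without any other type of complementary treatment".
- **A reader might want stratification by medication, or exclusion of families with earlier parent training.** Both are design preferences; nothing in the documents makes their absence an error.

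**Conclusion.** The point holds in a limited form. The protocol knowingly mixes children treated and untreated at entry, balances on age alone, and makes adjustment depend on preliminary data without naming medication. This creates no expected bias and leaves the nominal error rates intact for the arms as randomised. It gives up precision and leaves room for selective adjustment.

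With half the children medicated at entry and a residual variance of 0.64, the loss is about 2%, 5% or 11% of the standard error for gaps of 0.3, 0.5 or 0.8 SD. In the most favourable case the half-width falls by 0.453 − 0.405 = 0.048 SD. Prevalence, gap and residual variance are all assumptions. The improvement is modest but nearly free. The naive label needs only a wording correction.

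**What to change.** 1. In Additional analyses, and in the Outcomes part of Statistical methods to match, replace data-dependent adjustment of the primary comparison with one fixed model. Covariates: baseline score, age stratum and medication at entry (yes/no). Any other adjusted or subgroup analysis can remain, labelled exploratory.
2. State that medication at entry is recorded at the baseline assessment, before the allocation envelope is opened. Drug treatment started after allocation is a post-randomisation event. It should be reported by arm and not entered as a covariate in this model.
3. In Background and rationale, change the description of the third group from naive to usual care, to agree with the Abstract, Choice of comparators, Interventions and Concomitant care.

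The cost is one degree of freedom for the medication covariate and a few changed sentences. These treatments are already to be reported, so little or no new data collection is needed.
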